#### 2.4.3. Fitness Tracker

Physical activity is assessed daily by supplying each patient uses a commercial fitness tracker (Fitbit charge 3™ (Fitbit Inc., San Francisco) that will be linked to her smartphone (54). Study personnel assists the patients and – if required – their associate to install the smartphone app and to setup the measurements. The patients are requested to transcribe the measurements of their fitness tracker into their study diary weekly. Those values are shown in **Table 3**.

**Table 3 T3:** Measurements with the fitness tracker.

Description	Abbreviation	Registration interval	Unit
**Core stats**		**Daily**	
Steps taken		Daily	Count
Resting heart rate	RHR	Daily	Beats per minute
Calories burned	Cal	Daily	Kcal
**Workout stats**		**Real-time**	
Elapsed time		Real-time	Minute
Distance covered		Real-time	Km
Calories burned		Real-time	Kcal
Average heart rate	øHR	Real-time	Beats per minute
Maximum heart rate	HRmax	Real-time	Beats per minute

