### 2.9 Sample Size Calculation and Statistical Analyses

The Institute for Medical Biometry, Epidemiology and Medical Informatics (IMBEI) Saarland University is supporting the sample size calculation, study design, data management and evaluation using PASS 2019 (NCSS, LLC, Kaysville, Utah, USA) and SPSS (Version 27 IBM SPSS Statistics, Armonk, New York, USA). Data were collected by using Excel 2019 (Microsoft, Redmond, USA). A sample size of 110 produces a two-sided 95% confidence interval with a distance from the mean to the limits that is equal to 2.835 when the estimated standard deviation is 15.0. A sample size of 110 produces a two-sided 95% confidence interval with a width equal to 0.187 when the sample proportion is 0.50.

Continuous measures are presented as means ± standard deviations (SD) or medians (range). Categorical variables are presented as frequencies (percentage). For continuous variables normality is tested using Shapiro-Wilk-Test. In case of non-rejection of normality two-group comparisons are due to the t-test for two independent samples. For more than two groups, comparisons are due to one-way Analysis of Variance (ANOVA). Comparing two repeated measurements, t-test for 2 dependent samples is used and for more than two we use repeated measures ANOVA. In case of rejection of normality, Mann-Whitney U-test, Kruskal-Wallis-test, Wilcoxon test for two dependent samples and Friedman-test are used, respectively. For group comparisons considering categorical variables the chi-squared test and for repeated measures McNemars’s test are applied. Considering possible confounding we use subgroup analyses for categorical subgroups or propensity-score-matching otherwise. Statistical significance will be calculated using appropriate statistical methods with two-sided p-values < 0.05. The statistical analyses are explorative, so there will be no correction for multiple testing.

Data cleanup will include tests for missing data and plausibility. Depending on the degree of incompleteness or lack of accuracy, all, or some of the data from a patient will be excluded from further evaluation. In the case of a study drop out prior the last follow up visit, the patient’s data will only be included, and tests will be performed to identify potential predictors for a study drop-out (e.g., age or weight) that might introduce a bias. The risk of bias will be discussed in any publications of the data.

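### Whole-patient exclusion, an unfinished drop-out rule and complete-case tests over five visits discard observed data; the multi-visit results lose precision and may over-represent patients who tolerate therapy.

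*Protocol article*

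**What the plan says.** All of the relevant text is in section 2.9 (Sample Size Calculation and Statistical Analyses).

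- **Exclusion at data cleanup:** "Depending on the degree of incompleteness or lack of accuracy, all, or some of the data from a patient will be excluded". The sentence sets no threshold and does not say who decides between all and some.
- **Drop-out before the last visit:** the patient's "data will only be included, and tests will be performed to identify potential predictors for a study drop-out". The condition that should follow the word *only* is not there.
- **Tests:** two repeated measurements are compared with a paired test; "for more than two we use repeated measures ANOVA". If normality is rejected, the Friedman test takes its place. No mixed model, imputation or weighting is named.
- **Precision:** "A sample size of 110 produces a two-sided 95% confidence interval with a distance from the mean to the limits that is equal to 2.835". The SD behind this figure is put at 15.0. No allowance for loss is stated.
- **Safeguards:** predictors of drop-out are to be tested, and the risk of bias is to be discussed in publications. Section 2.4.1 adds that staff check the diary for completeness and accuracy at each follow-up visit.

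The abstract and section 2.4.2 fix the number of occasions at five: baseline and months 3, 6, 9 and 12.

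**The concern.** The study sets out to describe how physical, psychological and immunological measures develop over the first year of therapy. That calls for comparisons across all five visits, and there the plan works against itself in three ways.

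1. Incompleteness alone may remove a whole patient, including laboratory values, questionnaires and body composition that are perfectly valid.
2. The drop-out sentence does not tell the analyst what to do with a patient who leaves early.
3. Repeated measures ANOVA and the Friedman test, in their standard form, drop a patient who lacks any one of the values compared. A patient seen at four of five visits contributes nothing to them.

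Baseline precedes therapy and follow-up runs through it. Each visit includes a treadmill test that is ended by symptoms or exhaustion (section 2.4.2). A link between missing values and how the patient feels is therefore plausible. If it exists, discarding incomplete patients selects as well as shrinks the sample. With no exclusion threshold fixed in advance, exclusions made after associations are seen could not be shown to be neutral.

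**Working it through.** **Inputs from section 2.9:** n = 110, SD = 15.0, half-width 2.835. **From section 2.4.2:** five visits, so four follow-ups. **Assumed, because the protocol gives none:** the proportion m of patients missing each follow-up.

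**1. The plan's own figure.** Half-width = t(0.975, n−1) × SD/√n = 1.982 × 15/√110 = 1.982 × 1.430 = 2.835. It reproduces, but only if all 110 patients contribute.

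**2. Patients with all five values.** Baseline is taken as complete.
- Misses independent across visits: 110 × (1−m)^4.
- The same patients always miss: 110 × (1−m).

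| m | Independent: n, half-width | Same patients: n, half-width |
|---|---|---|
| 5% | 90, 3.14 | 104, 2.92 |
| 10% | 72, 3.52 | 99, 2.99 |
| 15% | 57, 3.98 | 93, 3.09 |

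For m = 10%: 110 × 0.9^4 = 72.2 and 1.994 × 15/√72 = 3.52; 110 × 0.9 = 99 and 1.984 × 15/√99 = 2.99. The half-width is then 24% (3.52/2.835) or 6% (2.99/2.835) larger than stated. Real misses usually cluster within patients, so a value between the two columns is more likely than the independent one.

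**3. Bias, by simulation.** Assumptions: five visits, SD 15, within-patient correlation 0.6, drop-out more likely when the last observed value is worse, no difference between therapies.
- With 10 to 30% lost and log-odds of drop-out rising by 0.5 to 1.0 per SD, completer-only visit means were 0.4 to 3.1 points too favourable (0.03 to 0.2 SD). The 12-month change was off by only 0.1 to 0.5 points.
- With heavier loss (58 to 69 completers of 110; log-odds 0.7 to 1.0 per SD), completer-only means were off by 0.17 to 0.35 SD and mean change by at most about 0.05 SD. A likelihood analysis of all observed values was off by at most 0.014 SD.

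Change is little affected because selection moves all five visit means by nearly the same amount.

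**4. When change is biased too.** Suppose half the patients have chemotherapy, declines are 0.8 SD with and 0.1 SD without it, and completeness is 50% and 85%.
- True mean change: 0.5 × (−0.8) + 0.5 × (−0.1) = −0.45 SD.
- Completers: (0.25 × (−0.8) + 0.425 × (−0.1))/(0.25 + 0.425) = −0.36 SD.

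The change within each therapy is unbiased in this example; only the pooled average shifts.

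**The case against.** Much of the case on the other side stands.

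- **The plan foresees the problem.** Tests for drop-out predictors, a bias discussion and diary checks are all stated. They can reveal selection. They do not correct an estimate, and the drop-out tests do not address a visit missed by a patient who stays in the study.
- **Precision is not lost everywhere.** Paired t, Wilcoxon and McNemar tests need only the two values compared, and baseline estimates do not depend on later visits.
- **The larger bias figures concern completer-only means.** Section 2.9 does not prescribe descriptive means on completers. The named tests address change, where bias was small. The therapy example is an illustration, and section 2.9 does name subgroup analyses and propensity-score matching for confounding.
- **Thresholds may sit in a fuller document, and the analyses are declared exploratory.** That lowers the severity. It does not complete the drop-out sentence or alter the tests that are fixed here.

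Three stronger readings are tempting and are not supported.

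1. A reader might infer that the weekly series cannot be analysed, since the tracker is read out weekly ("The patients are requested to transcribe the measurements of their fitness tracker into their study diary weekly") and some 52 weeks with every value present would be rare. No test across all weeks is planned. Means between visits would fit the named tests, and how weekly data are summarised is commonly left to the fuller plan.
2. A reader might infer that the results do describe the patients who cope best. The protocol gives neither a drop-out rate nor reasons, so the direction is plausible but not shown.
3. A reader might take the drop-out sentence to mean inclusion only if complete. A patient who leaves early cannot be complete, so that reading would contradict inclusion altogether. A clause has evidently been lost.

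**Conclusion.** The point holds in a limited form and should be fixed. Three things rest on the text alone: incompleteness can remove a whole patient, the drop-out rule has no condition, and the only methods named for more than two visits use complete patients.

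The size depends on assumed missingness. At 10% per follow-up, 72 to 99 of 110 patients remain and the half-width is 3.52 to 2.99 instead of 2.835. If levels are reported on completers, they may be too favourable by a few hundredths to about a third of an SD, depending on how much is lost and how strongly loss follows poor values. Mean change is nearly unbiased unless decline and completeness both differ by therapy. Selection towards patients who tolerate therapy is a risk and not an established fact.

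**What to change.** In section 2.9, or in a dated analysis plan written before associations are examined:

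1. State that all observed values of all enrolled patients are analysed, and that single values are removed only for documented measurement error, decided without sight of the associations.
2. Complete the drop-out sentence: drop-outs contribute all data up to drop-out.
3. For comparisons across the visits, replace repeated measures ANOVA and Friedman by a linear mixed model with visit as a categorical factor and therapy as a covariate, on the log scale for skewed markers.
4. Report n per visit, and give the complete-case result as a sensitivity analysis.

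Keep the drop-out predictor tests and the bias discussion.

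The cost is wording and slightly more analysis work in the SPSS version already named; no new patients or data are needed. The downside is that the mixed model relies on values being missing at random given the observed data. That cannot be verified, but it is weaker than what a complete-case analysis generally needs.

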## 3 Discussion

The BEGYN study will provide a holistic insight into the physical activity in relation to the physiological and psychological dynamics during the first year after diagnosis of non-metastatic breast cancer. The complex interplay between the underlying disease, antineoplastic therapy and individual constitution affects the patient *in toto*. Thus, therapeutic approaches must not be limited to surgery, antineoplastic medication, radiotherapy and psychological intervention alone, but should include the motivation for supportive activities such as exercise, which has great effect on the quality of life and prognosis (35, 99–101). A better knowledge of biomarkers is a prerequisite to assess the effects of complementary therapies and to develop personalized strategies for rehabilitation, e.g., regarding the type and dose of exercise (9). Therefore, the BEGYN study unites multiple validated assessments, allowing cross-linking analyses between the level of physical activity, cardiopulmonary fitness, body composition, biochemical measurements, an in-depth immune status including quantification of circulating lymphocyte subpopulations, mRNA expression and cytokine profiles and an extensive evaluation of psychological factors.

### 3.1 Novelty of the Approach

Whereas most studies investigating the influence of physical activity in breast cancer patients focus on specific activities for three months or less, the BEGYN study will quantify the daily physical activity and cardiorespiratory fitness of breast cancer patients based on objective measurements in the context of the oncological therapy for 12 months after diagnosis. Multiple studies have shown that physical activity can have positive effects in breast cancer patients (4–6, 33–35, 37). Guidelines recommend physical activity during breast cancer treatment, in example in the United States (102), in Great Britain (103), in Germany (39) and others. In particular, physical activity appears to have a positive effect on breast cancer associated fatigue syndrome (3) and on the overall quality of life (104). However, multiple aspects including the underlying mechanisms remain poorly understood. The BEGYN study will contribute important data to understand the influence of physical activity on the dynamics during the first year of breast cancer treatment and may reveal potential modifiers of the patient’s well-being.

#### 3.1.1 Holistic Approach

To our knowledge, the BEGYN study is one of the largest studies with a very broad approach in breast cancer patients that will allow to identify associations between physical, psychological and laboratory variables, thus linking aspects that are often studied separately in breast cancer patients. Regarding the assessment of physical activity, it will be of particular interest to discuss the results of the BEGYN study in the light of other ongoing highly innovative studies such as the PROTECT study which also includes patients with colorectal cancer and lung cancer (6). One of the major strengths is the continuous recording of the patient’s physical activity and well-being by diary and by use of a fitness tracker since physical activity encompasses not only explicit sports activities, which may last a few hours per week, but also activity during everyday activities. Various forms of physical activity have been proposed, such as yoga, Tai Chi Chuan, Nordic walking, jogging, weight training, cycling, dancing and many others (20, 36, 37, 47). However, it has been claimed that individualized recommendations are needed to meet the needs of the patient (6, 105). By using the concept of metabolic equivalents (MET), the BEGYN study will allow comparing effects of physical activities of similar intensities independent of the type of exercise. Since nutrition, food supplements and lifestyle may significantly influence the effects of exercise and antineoplastic therapies, these variables are assessed by using questionnaires and the self-assessment diary.

#### 3.1.2 One Year Study Schedule

The BEGYN study will yield an overview on a relatively long period of 12 months after diagnosis, starting before any specific antineoplastic therapy. Thus, the patient will typically be observed beyond the initial steps of therapy, which are also often associated with psychoemotional distress. This may give insight into predictors of a more favorable long-term management towards a new physical and psychological balance. Moreover, the 12 months study period will reduce potential artifacts due to seasonal effects which can, in example, influence outdoor activities and Vitamin D concentrations. The role of Vitamin D in carcinogenesis and cancer therapy is still under debate. Importantly, serial measurements of 2,5 OH Vitamin D concentrations in peripheral blood and assessment of therapeutic Vitamin D intake may give insight into the role of Vitamin D metabolism and may also provide data on the interaction between antineoplastic therapy and Vitamin D. In addition, the BEGYN study will yield serial selenium concentrations and insight on the consumption of selenium by the patients, which often is provided as a self-medication, causing significant financial burden for some patients.

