**Methods:**

The prospective observational BEGYN study will include 110 non-metastatic breast cancer patients. The patients will be assessed during a base line visit prior to the initiation of the antineoplastic therapy and after 3, 6, 9 and 12 months. The physical activity will be measured using a fitness tracker and a self-assessment diary during the entire study. Each visit will include the assessment of (i) cardiorespiratory fitness measured by spiroergometry, (ii) body composition, (iii) psycho-emotional parameters (quality of life, mental health, fatigue, depression, distress, anxiety, well-being), and (iv) extensive blood tests including routine laboratory, vitamin D, selenium and immunologically relevant biomarkers (e.g., leukocyte subpopulations and cytokine profiles).

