### 2.6 Nutritional Habits, Intake Of Food Supplements, Self-Medications, and Lifestyle

According to the guideline, a Mediterranean diet was recommended to all patients (39). Nutritional habits were assessed using a questionnaire with a focus on characteristic dietary patterns. In addition, sleeping, smoking, and drinking habits, the use of food supplements and self-medication as well as exposure to sunlight and use of sun protection were assessed using questionnaires and the self-assessment diary, respectively.

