**Biochemical parameters**				
Sodium	quarterly	Li-Heparin-Plasma	mmol/l	135 – 145
Potassium	quarterly	Li-Heparin-Plasma	mmol/l	3.5 – 5.1
Calcium	quarterly	Li-Heparin-Plasma	mmol/l	2.2 – 2.6
Magnesium	quarterly	Li-Heparin-Plasma	mmol/l	0.66 – 1.07
Iron	quarterly	Li-Heparin-Plasma	µg/dl	33 – 193
Creatinin	quarterly	Li-Heparin-Plasma	mg/dl	0.50 – 0.90
Urea	quarterly	Li-Heparin-Plasma	mg/dl	17 – 48
Uric acid	quarterly	Li-Heparin-Plasma	mg/dl	2.5 – 5.7
Glucose	quarterly	Li-Heparin-Plasma	mg/dl	60 – 100
Protein	quarterly	Serum	g/l	66 – 87
Albumin	quarterly	Serum	g/l	35 – 52
Cholesterol	quarterly	Li-Heparin-Plasma	mg/dl	<200
Triglycerides	quarterly	Li-Heparin-Plasma	mg/dl	<150
CK	quarterly	Li-Heparin-Plasma	U/l	0 – 170
ASAT	quarterly	Li-Heparin-Plasma	U/l	0 – 35
ALAT	quarterly	Li-Heparin-Plasma	U/l	0 – 35
gamma-GT	quarterly	Li-Heparin-Plasma	U/l	<40
Alkaline phosphatase	quarterly	Li-Heparin-Plasma	U/l	35 – 104
Bilirubin	quarterly	Li-Heparin-Plasma	mg/dl	<1.2
Lipase	quarterly	Li-Heparin-Plasma	U/l	13 – 60
LDH	quarterly	Li-Heparin-Plasma	U/l	0 – 262
CRP	quarterly	Li-Heparin-Plasma	mg/l	0.0 – 5.0
HbA1c	quarterly	EDTA	%	<6.0
LDL-Cholesterol	quarterly	Li-Heparin-Plasma	mg/dl	<130
HDL-Cholesterol	quarterly	Li-Heparin-Plasma	mg/dl	45 – 65
VLDL-Cholesterol	quarterly	Li-Heparin-Plasma	mg/dl	<35
Interleukin-6	quarterly	Li-Heparin-Plasma	pg/ml	<7
Selenium	quarterly	Serum	µg/l	50 – 120 (67)
Vitamin D-25-OH	quarterly	Serum	ng/ml	30 – 100 (68)

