### 3.3 Ethics and Dissemination

The study is carried out at the Department for Gynecology, Saarland University Medical Center and has been approved by the ethics committee of the Medical Association of Saarland (study # 229/18). Written consent is obtained from the patient in accordance with the Declaration of Helsinki. Any amendment to the protocol will require the formal modification and approval by the same local ethics committee that approved the study prior to implementation and will be described transparently in subsequent reports. This study is registered at German Clinical Trials Register (DRKS) (DRKS00024829). Patient recruitment took place between September 2019 and January 2021 and data collection will continue until March 2022.

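### The 12-month period matches season only for baseline versus month 12 and for full-year averages; contrasts at months 3, 6 and 9 and same-date activity–vitamin D associations keep a seasonal component that the tests in section 2.9 do not remove

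*Protocol article*

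**What the plan says.** The protocol article names season as an influence on two of its own variables and relies on the study length to lessen it: "the 12 months study period will reduce potential artifacts due to seasonal effects which can, in example, influence outdoor activities and Vitamin D concentrations" (section 3.1.2). The same paragraph then expects insight from serial vitamin D measurements, including their interaction with antineoplastic therapy.

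Visits take place "prior to the initiation of the antineoplastic therapy and after 3, 6, 9 and 12 months" (abstract, Methods), and Table 5 lists vitamin D as a quarterly measurement. Activity is recorded continuously: "The physical activity will be measured using a fitness tracker and a self-assessment diary during the entire study". On timing, section 3.3 states: "Patient recruitment took place between September 2019 and January 2021 and data collection will continue until March 2022".

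For longitudinal comparisons section 2.9 says: "Comparing two repeated measurements, t-test for 2 dependent samples is used and for more than two we use repeated measures ANOVA". Wilcoxon and Friedman tests are used if normality is rejected. For confounding it says: "Considering possible confounding we use subgroup analyses for categorical subgroups or propensity-score-matching otherwise". Season is not named. Section 2.6 records that "exposure to sunlight and use of sun protection were assessed using questionnaires and the self-assessment diary", together with supplement use.

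**The concern.** A year of follow-up brings a patient back to her baseline season once, at month 12. Her month 3 and month 9 visits are a quarter-cycle away, and month 6 falls in the opposite season. The serial vitamin D readings and visit-to-visit changes in activity that section 3.1.2 wants to interpret are mostly these intermediate contrasts, and the study length does not season-match them.

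The listed methods do not make up for this. A paired t-test, repeated measures ANOVA, Wilcoxon or Friedman test compares visits without any covariate that varies by visit. Subgroups and propensity-score matching work between patients. Subgrouping by season of enrolment would even make matters worse for visit contrasts, because within such a subgroup visit and season move together.

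Two kinds of result are at stake. Part of a change between visits could be a calendar effect read as an effect of therapy or exercise. And since the article itself says that season drives both outdoor activity and vitamin D, the two can correlate on a given date without any direct link.

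**Working it through.** **The plan's own figures.** The article gives no figure on season. Its precision statements in section 2.9 reproduce: t(0.975; 109) × 15/√110 = 2.835, and 2 × 1.96 × √(0.25/110) = 0.187.

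**Inputs.** From the documents: visits at months 0, 3, 6, 9 and 12; entry from September 2019 to January 2021, which is 17 calendar months with September to January twice and February to August once. Assumed, because the article does not give them: even accrual, a seasonal effect shaped as an annual cosine of amplitude A, and a peak between mid-July and mid-August.

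**Step 1, one patient.** The largest purely seasonal change over v months is 2A·|sin(πv/12)|.

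| Month | Largest within-patient seasonal change from baseline |
|---|---|
| 3 | 1.41A |
| 6 | 2.00A |
| 9 | 1.41A |
| 12 | 0 |

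The mean over 12 consecutive months is 0, as is the mean over visits 0, 3, 6 and 9. A mean over all five visits counts the baseline season twice and keeps up to 0.20A.

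**Step 2, the cohort.** For even entry over 17/12 of a cycle, the mean seasonal vector has length |sin(17π/12)/(17π/12)| = |sin(4.451)|/4.451 = 0.217 and at baseline points to mid-November. The mean offset at each visit is 0.217A × cos(angle from the peak).

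| Assumed peak | Month 0 | Month 3 | Month 6 | Month 9 | Month 12 | Largest shift from baseline | Month 9 minus month 3 |
|---|---|---|---|---|---|---|---|
| mid-July | −0.11A | −0.19A | +0.11A | +0.19A | −0.11A | 0.30A | 0.38A |
| 1 August | −0.06A | −0.21A | +0.06A | +0.21A | −0.06A | 0.27A | 0.42A |
| mid-August | 0 | −0.22A | 0 | +0.22A | 0 | 0.22A | 0.43A |

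A month-by-month tabulation with the peak at the turn of July to August gives shifts from baseline of −0.16A, +0.11A, +0.27A and 0. With linearly rising or falling accrual the largest gap between visits stays at 0.42A to 0.43A. Exactly 12 months of even accrual would give a shift of 0 at every visit.

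**Step 3, how far visit and season are tied.** With even accrual the shares of winter/spring/summer/autumn are:

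- baseline and month 12: 29/18/18/35%
- month 3: 35/29/18/18%
- month 6: 18/35/29/18%
- month 9: 18/18/35/29%

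Visit number explains about 4% of the seasonal variance (Cramér's V 0.17), so about 96% is left from which to estimate season separately.

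**Step 4, size on a scale.** If season explains 10% to 30% of a marker's variance (assumed), A = √(2 × share) SD, which is 0.45 to 0.77 SD. The 0.43A gap is then 0.19 to 0.33 SD, and a 0.27A shift from baseline is 0.12 to 0.21 SD. The half-width behind the sample size is 2.835/15 = 0.19 SD. For vitamin D with A of 5 to 10 ng/ml (assumed), 0.43A is 2.2 to 4.3 ng/ml.

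**Step 5, same-date association.** If season explains 10% of step variance and 30% of vitamin D variance, with the same timing (assumed), the induced correlation is √(0.10 × 0.30) = 0.17. With n = 110 the two-sided 5% threshold is about |r| = 0.187. By Fisher's z, atanh(0.173) × √107 = 1.81, so such a correlation would be called significant about 44% of the time instead of 5%. A lag between the two seasonal cycles lowers this.

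**The case against.** The sentence in 3.1.2 promises only a reduction, and it belongs to an argument that compares this study with studies of three months or less. Against that comparator it is correct, both for baseline versus month 12 and for full-year tracker and diary data. This stands: the sentence is incomplete rather than false.

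A reader might infer from the 17-month window that season is confounded with visit number. The documents do not support that. Entry over 17 months puts every calendar month at every visit, and only the doubled September to January leaves an imbalance, about 4% of the seasonal variance under the accrual patterns tried. Season can be separated from visit by means of the visit dates.

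The magnitudes depend on assumed amplitude, peak and accrual. The 0.43A figure is the least favourable pair of visits; shifts from baseline are smaller, and with a mid-August peak the mean shift at month 6 is zero. An expected correlation of 0.17 lies below the significance threshold at a single visit. These limits also stand.

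Finally, section 2.9 provides for confounding, calls the analyses explorative, and may be expanded in a plan that is not shown. This stands in part. Season subgroups, or matching that includes visit date, could serve a comparison at one visit, though with even accrual the smallest season at baseline would hold about 19 of 110 patients. Neither route adjusts a within-patient change. The point is thus not a missing covariate list: the longitudinal methods that the article does state do not deliver the reassurance that 3.1.2 offers.

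**Conclusion.** The concern holds in limited form. The study length gives season matching for baseline versus month 12 and for full-year averages, and for nothing else. Contrasts involving months 3, 6 and 9 keep a seasonal part: up to 1.4A to 2.0A for an individual patient, at most about 0.2A to 0.3A as a cohort-mean shift from baseline, and about 0.38A to 0.43A between months 3 and 9. The cohort figures assume even accrual and a peak between mid-July and mid-August. Markedly uneven accrual could raise or lower them, and monthly accrual is not reported. Same-date associations between activity and vitamin D are exposed whatever the balance across visits.

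That the 12-month design fails against season, or that visit effects cannot be told from season, would be too strong. Season is partly imbalanced across visits, and the imbalance can be corrected in the analysis. Recruitment is closed, so the analysis is where it has to be done.

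**What to change.** - For activity and vitamin D, replace or supplement repeated measures ANOVA with a linear mixed model containing visit plus the sine and cosine of visit date (day of year). For vitamin D, add recorded supplement use. Fit the same model to the mood measures as a sensitivity analysis.
- Put the same two season terms into every model of the association between activity and vitamin D.
- In section 3.1.2, limit the claim to baseline versus month 12 and to full-year averages.
- Report the number of patients per calendar month at each visit, so that the assumed accrual can be replaced by the real one.

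The cost is a change of model class, since terms that vary by visit date cannot simply be added to the paired, repeated measures ANOVA or Friedman tests, and two extra parameters per model. It needs only the visit dates and supplement data the study already collects.
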